### **Intervention**

The intervention was developed in concert with clinical experts from both primary care and cardiology, as well as experts in knowledge translation and medical decision-making. Personalized letters sent via post to the patient and their family physician at one, five, eight, and eleven months after their angiogram, signed by the interventional cardiologist (see Additional file 1: Appendix A for prototype). The letter for the family physician names the patient and provides brief evidence in support of long-term medication use for these patients. This was reviewed and edited with a series of family physicians from a different area of the province.

The patient letter provides a review of the importance and role of each of the cardiac medications and urges short- and long-term adherence (see Additional file 1: Appendix B for prototype). This educational aspect is designed to address knowledge and beliefs about medication use as a potential cause of poor adherence. The intervention explicitly encourages discussion of medication adherence with the family physician by asking patients to bring the letter to their family physician. It also asks patients to deliver the final page of their letter to their pharmacist; this page is written to the pharmacist urging them to participate in promoting long-term adherence. The intention is to facilitate recurrent discussions with primary care providers that emphasize long-term adherence and to address coordination of care and continuity of information as barriers to medication persistence. This letter was developed with iterative evaluations of understanding and acceptability amongst a series of cardiology patients at the HIU. The language in the patient letter is simplified to a grade six-level.

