### **Allocation**

The randomization schedule was computer-generated by a statistician independent of the study, using a permuted block design with randomly varying block lengths of four, six, or eight. Eligible patients are randomly allocated to one of the two treatment arms. Although enrolment of more than one patient treated by a particular family physician is expected to occur infrequently, randomization will be carried out to ensure that, once a patient from any family physician is randomized, all future patients seen by that family physician will automatically be assigned to the same arm. This is necessary to avoid contamination (with one family physician having patients in different intervention arms). Roughly one-half of patients will be allocated to each study arm (the actual allocation ratio will depend on the size of the clusters). Based on pilot data, we anticipate that approximately 10% to 15% of patients will not have a family physician. In keeping with the pragmatic design of the trial, a patient without a family physician will be included (receiving only the patient-level intervention).

Randomization is delayed by one week (after the angiogram) to permit time to identify and exclude patients with in-hospital death. Randomization will continue until the target sample size is achieved. The anticipated duration of enrolment is 15 months. The allocation sequence will be concealed from the investigators and outcome assessors; only the study coordinator who will be sending out the letters will have access to the un-blinded allocation list.

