### **Data collection**

Baseline patient characteristics will be obtained from standard patient-registry information at the HIU. This includes demographic information, comorbidities, and the findings at the time of angiography.

Outcomes will be assessed 3 and 12 months post-index angiogram through patient phone calls by a research coordinator associated with the HIU who will be trained expressly for this function. The research coordinator conducting the phone calls will not have access to the allocation list. The calls are made on behalf of the treating cardiologist at the HIU, and all patients will be encouraged to review cardio-protective meds with their family physician. The phone call follow-ups will ask patients to list their current, daily medications (and doses) without specific prompting in order to reduce bias. Attempts will be made to contact patients for a maximum of 30 days prior to being considered lost-to-follow-up. Reasons for loss-to-follow-up will be tracked.

For a sample of patients aged 65 and older, the Ontario Drug Benefit database will be used to examine the accuracy of the self-reported primary outcome and to further evaluate adherence using the medication possession ratio over the preceding year, which has been shown to be associated with both pill counts and clinical effects [47].

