### **Analysis**

Descriptive statistics will be calculated for all variables of interest: continuous variables with a normal distribution will be summarized using means and standard deviations (medians and inter-quartile ranges in the case of skewed distributions), whereas categorical variables will be summarized using frequencies and proportions.

We hypothesize that the intervention will result in a greater proportion of patients who report taking each cardiovascular medication class of interest at 12 months post-angiography. The absolute difference in proportions will be calculated for all primary and secondary dichotomous outcomes, together with 95% confidence intervals adjusting for clustering by family physician [48]. The statistical significance of differences between arms will be evaluated using chi-squared tests, adjusted for clustering by family physician.

Exploratory multivariable analyses will be carried out using generalized estimating equations (GEE) to identify potential baseline predictors of adherence. Potential effect modification by treatment—medical management versus coronary artery bypass graft (CABG) versus angioplasty—and attendance at cardiac rehabilitation will be explored by including interactions between these two variables and group. It is plausible that this analysis will suggest a need for tailored interventions for these subgroups. A further exploratory analysis will be conducted focusing on patients who reported taking all five cardiac medication classes and had perfect MMAS scores at three months using a multivariable model to examine covariates predicting late-onset discontinuation. In addition, a planned sensitivity analysis will exclude those patients who did not have a family physician, as we would expect such patients to be more likely to discontinue their cardiac medications.

Analyses will be performed on an intention-to-treat basis. No interim analyses are planned. All analyses will be carried out using the SAS Version 9.2 statistical program (SAS Institute, Cary, NC, USA).

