### **Sample size**

The sample size for this design is based on the following assumptions: an assumed absolute increase in the proportion of patients taking all four cardiovascular medication classes of 11% at twelve months post-STEMI; an estimated control group proportion of 50%, and a variance inflation factor of 1.02 (derived from an intra-cluster correlation coefficient of 0.019 calculated from data in the SMART-AMI registry and assuming an average cluster size of 1.2 based on pilot data). To achieve 80% power to detect a significant main effect of the intervention using a Chi-squared test at the 5% level of significance, 652 patients would be required. We will randomize 815 patients to account for an estimated participation rate of 80% at the 12-month follow-up. This dropout rate is conservative based on similar studies at the HIU where the participation rate has been greater than 90% over even longer time periods [40].

The expected effect size is slightly higher than the effect seen in the previous Canadian trial to account for the fact that the intervention is multifaceted (directed at both physician and patient) and occurring later post-STEMI (reducing the expected control group rate and therefore the possibility of a ceiling effect). Based on this sample size calculation, and the rate of STEMI patients presenting to the HIU, we anticipate that it will take approximately 15 months to complete the recruitment for this study.

We will use a kappa statistic to assess agreement between the self-report of the primary outcome and the corresponding objective data from the Ontario Drug Benefit database. Based on an anticipated overall proportion of 56% at 12 months (average of intervention and control arm) and an anticipated kappa of 0.88, we would consider acceptable agreement if the lower limit of the 95% confidence interval around kappa does not drop below 0.80. Therefore we will evaluate validity of the primary outcome in a random selection of 138 patients aged 65 or greater.

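### Cardiac rehabilitation attendance, very probably settled after allocation, is planned as an effect modifier; its subgroup effects are not randomised comparisons and should not support tailoring

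*Protocol article*

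**What the plan says.** The Analysis section introduces its exploratory models with "Exploratory multivariable analyses will be carried out using generalized estimating equations (GEE) to identify potential baseline predictors of adherence". It then adds effect modification by type of treatment (medical, CABG or angioplasty) and by rehabilitation: "attendance at cardiac rehabilitation will be explored by including interactions between these two variables and group". The intended reading follows at once: "It is plausible that this analysis will suggest a need for tailored interventions for these subgroups".

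Three other places bear on the timing:

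- **Allocation:** "Randomization is delayed by one week (after the angiogram) to permit time to identify and exclude patients with in-hospital death".
- **Intervention:** "Personalized letters sent via post to the patient and their family physician at one, five, eight, and eleven months after their angiogram". The section on the timing of the letters adds a patient postcard at two months.
- **Data collection**, on the baseline registry data: "This includes demographic information, comorbidities, and the findings at the time of angiography". Rehabilitation is not named there.

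Rehabilitation is mentioned nowhere else in the article. When and how attendance is recorded is not stated, and nothing limits it to status before allocation.

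**The concern.** A subgroup comparison inherits the protection of randomisation when the subgroup is fixed before allocation, or at least cannot be altered by it. Attendance is a behaviour, and most or all of it would fall after the first week. The letters could reach it through the family physician: "The intervention explicitly encourages discussion of medication adherence with the family physician by asking patients to bring the letter to their family physician". A patient who is more engaged, or who sees the physician more often, may be more likely to attend.

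If the letters bring some patients into rehabilitation who would otherwise have stayed away, attenders in the intervention arm are a different mix of people from attenders in the control arm. The same holds for non-attenders. A difference between arms within either stratum then reflects that mix as well as any effect of the letters on medication use.

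What is at stake is the practical conclusion that the protocol attaches to this analysis. A recommendation to treat attenders and non-attenders differently could rest on selection. A larger sample would not remove the problem.

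**Working it through.** **Timing.** The protocol gives no figure for this point, so the passages are set side by side.

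1. Allocation is one week after the angiogram (Allocation).
2. The first letter goes out at one month (Intervention).
3. The variable is attendance, not referral (Analysis), and it is absent from the baseline data described (Data collection).

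Attendance is therefore very probably determined after allocation, and may largely overlap with the letters. This is an inference; the article does not say so.

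**Illustration 1: by hand.** All inputs are assumptions. The letters change nobody's medication use. Patients are of three kinds: always attend (share *a*, 65% adherent), attend only because of the letters (share *c*, 50% adherent), and never attend (share 1 - *a* - *c*, 40% adherent). Take *a* = 0.40 and *c* = 0.10.

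- Attenders, control: 65%. Attenders, intervention: (0.40 × 0.65 + 0.10 × 0.50) / 0.50 = 0.31 / 0.50 = 62.0%. Apparent effect: -3.0 points.
- Non-attenders, control: (0.10 × 0.50 + 0.50 × 0.40) / 0.60 = 0.25 / 0.60 = 41.7%. Non-attenders, intervention: 40%. Apparent effect: -1.7 points.
- Overall, both arms: 0.26 + 0.05 + 0.20 = 51%. Apparent effect: 0.
- Interaction (attenders minus non-attenders): -3.0 - (-1.7) = -1.3 points.

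For *a* from 0.30 to 0.50:

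| Rise in attendance (*c*) | Attenders | Non-attenders | Interaction |
|---|---|---|---|
| 0 | 0 | 0 | 0 |
| 5 points | -1.4 to -2.1 | -0.7 to -1.0 | -0.4 to -1.4 |
| 15 points | -3.5 to -5.0 | -2.1 to -3.0 | -0.5 to -2.9 |

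**Illustration 2: latent motivation.** These inputs are also assumptions. Motivation U is standard normal. A patient is adherent if 0.8U + e > 0, with e standard normal. Attendance depends on 0.7U plus noise, scaled to unit variance, and is 40% in controls. The letters have no effect on adherence. The results come from 4 million simulated patients.

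| Attendance with letters | Attenders | Non-attenders | Interaction |
|---|---|---|---|
| 50%, threshold lowered equally for all | -3.0 | -2.8 | -0.2 |
| 60%, threshold lowered equally for all | -5.8 | -5.8 | about 0 |
| 53%, letters bring in 30% of non-attenders with U < 0 | -9.7 | +3.1 | about -12.7 |

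An even shift distorts both stratum effects but hardly touches their difference. Uneven uptake, concentrated in less motivated patients, produces a false interaction although the letters helped nobody take more medication.

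**Scale.** The sample size rests on "an assumed absolute increase in the proportion of patients taking all four cardiovascular medication classes of 11% at twelve months post-STEMI", with 652 patients analysed and a variance inflation factor of 1.02. With an even split by attendance (an assumption), each of the four cells holds 652 / 4 = 163 patients. At proportions near 50%, the standard error of the interaction is √(1.02 × 4 × 0.25 / 163) = 7.9 points.

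**The case against.** The strongest reply has four parts.

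- **The planned quantity is the interaction.** When attendance rises evenly, its bias is close to zero. In the three-type illustration it is at most about 3 points, against a standard error of about 8. This stands. A reader might infer from the stratum shifts of -3 or -6 points that the interaction test is off by as much, but those figures do not show that. Only uneven uptake gives a large false interaction, and that scenario is an assumption too.
- **No effect of the letters on attendance is shown.** As described, they concern medication, the family physician and the pharmacist; rehabilitation is neither described content nor an outcome. This also stands. A reader might infer that the attendance-specific effects are certainly biased, but the documents support only that they may be. The assumed rises of 10 and 20 points have no source in the protocol, and the larger is nearly twice the 11-point effect assumed for the primary outcome.
- **The analysis is exploratory and cautiously worded.** This is true, and it limits the severity. The label warns about multiplicity and low power, however; it does not address selection after allocation, and the protocol still names a practical use for the result.
- **The timing may be defined elsewhere.** An article may leave the definition of attendance to a fuller document. If only status before allocation is meant, one sentence settles the matter.

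A reader might also extend the point to the comparison of CABG, angioplasty and medical management. The documents do not support this. Nothing in them indicates that procedures after the first week define that variable, and angiography findings are listed as baseline data.

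**Conclusion.** The point holds as a caution about one exploratory analysis. Rehabilitation attendance is very probably settled after allocation and could be influenced by the letters, so effects within attenders and non-attenders are not randomised comparisons. They may be biased if the letters change attendance. The interaction may be biased if that change is uneven across patients. If attendance does not change, there is no bias of this kind.

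No size can be drawn from the documents. In the illustrations, stratum effects move by roughly 1 to 6 points when the shift is even or modest. The interaction stays near zero or reaches about 3 points, and strongly uneven uptake gives about 13. The primary intention-to-treat comparison and the sample size are untouched. The planned step from this analysis to tailored interventions is what needs changing.

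**What to change.** - Report rehabilitation attendance by arm as a post-allocation measure. This also shows whether attendance differed between arms.
- Take attendance out of the interaction models that are meant to inform tailoring. Alternatively, keep it with an explicit statement that the contrast is non-randomised and that no tailoring conclusion will be drawn from it.
- Restrict effect modification to variables fixed at allocation, such as treatment received up to that point.
- If rehabilitation itself is of interest, use referral made before allocation, but only if it is already recorded. It is not among the baseline data described, so adding it could mean extra data collection.

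Apart from that last option, the cost is analysis-plan wording. The downside is that the attendance subgroup is given up as a causal question, which this design cannot answer without further assumptions.

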### **Sample size**

The sample size for this design is based on the following assumptions: an assumed absolute increase in the proportion of patients taking all four cardiovascular medication classes of 11% at twelve months post-STEMI; an estimated control group proportion of 50%, and a variance inflation factor of 1.02 (derived from an intra-cluster correlation coefficient of 0.019 calculated from data in the SMART-AMI registry and assuming an average cluster size of 1.2 based on pilot data). To achieve 80% power to detect a significant main effect of the intervention using a Chi-squared test at the 5% level of significance, 652 patients would be required. We will randomize 815 patients to account for an estimated participation rate of 80% at the 12-month follow-up. This dropout rate is conservative based on similar studies at the HIU where the participation rate has been greater than 90% over even longer time periods [40].

The expected effect size is slightly higher than the effect seen in the previous Canadian trial to account for the fact that the intervention is multifaceted (directed at both physician and patient) and occurring later post-STEMI (reducing the expected control group rate and therefore the possibility of a ceiling effect). Based on this sample size calculation, and the rate of STEMI patients presenting to the HIU, we anticipate that it will take approximately 15 months to complete the recruitment for this study.

We will use a kappa statistic to assess agreement between the self-report of the primary outcome and the corresponding objective data from the Ontario Drug Benefit database. Based on an anticipated overall proportion of 56% at 12 months (average of intervention and control arm) and an anticipated kappa of 0.88, we would consider acceptable agreement if the lower limit of the 95% confidence interval around kappa does not drop below 0.80. Therefore we will evaluate validity of the primary outcome in a random selection of 138 patients aged 65 or greater.

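### The validity check on the self-reported primary outcome is one kappa pooled over arms, which cannot show whether over-reporting differs between arms

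*Protocol article*

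**What the plan says.** The check is fixed in the protocol article under Sample size: "We will use a kappa statistic to assess agreement between the self-report of the primary outcome and the corresponding objective data", the objective source being the Ontario Drug Benefit database. The pass mark is stated: "we would consider acceptable agreement if the lower limit of the 95% confidence interval around kappa does not drop below 0.80". The planning inputs are pooled over arms: "Based on an anticipated overall proportion of 56% at 12 months (average of intervention and control arm) and an anticipated kappa of 0.88". The sample follows from them: "Therefore we will evaluate validity of the primary outcome in a random selection of 138 patients aged 65 or greater". No balancing of that sample by arm is mentioned.

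Data collection describes the same subsample and adds the medication possession ratio over the preceding year. Limitations names self-report as a caveat, offers this comparison (including the Morisky score) in response, and mentions the possession ratio again. None of these sections compares misclassification, or the outcome as defined from the database, between arms.

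On how the outcome arises, Intervention says: "The patient letter provides a review of the importance and role of each of the cardiac medications". Letters go out at 1, 5, 8 and 11 months over the interventional cardiologist's signature. At 3 and 12 months a coordinator without access to the allocation list telephones on behalf of the treating cardiologist. On the calls, Data collection says: "The phone call follow-ups will ask patients to list their current, daily medications (and doses) without specific prompting in order to reduce bias".

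**The concern.** Patients in the intervention arm know that they received letters going through each medication class, the last about one month before the 12-month call. They may list a class they no longer take because they know the answer expected, or recall the list better because the letters rehearsed it. Error of that kind is larger in one arm and adds directly to the difference in proportions. Error of equal size in both arms does not create a difference where none exists.

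A kappa over both arms measures the total amount of disagreement, not where it lies. The same value can come from harmless error spread evenly or from error concentrated in the intervention arm. If a lower limit of 0.80 is read as validating the outcome, part of a reported benefit could be better reporting rather than better persistence, and the stated check would not reveal it.

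**Working it through.** **1. Inputs, all from Sample size.** Overall proportion 56%; anticipated kappa 0.88; lower limit 0.80; validation n = 138; control proportion 50%; target effect 11 points. Allocation is roughly one-half to each arm, so 69 per arm is assumed.

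**2. Reproducing 138.** With both margins at 0.56:
- Chance agreement Pe = 0.56² + 0.44² = 0.5072.
- Observed agreement Po = 0.88 × (1 − 0.5072) + 0.5072 = 0.9409.
- Variance per patient = Po(1 − Po)/(1 − Pe)² = 0.9409 × 0.0591/0.4928² = 0.2291.
- n = 0.2291 × (1.96/0.08)² = 137.5, rounded up to 138.

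The figure reproduces. The planned kappa therefore tolerates 1 − 0.9409 = 5.9% disagreement over the whole sample.

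**3. An effect made wholly of over-reporting.** Assume that the database shows 50% on all four classes in both arms, that control self-report is exact, and that the intervention arm reports 61% (11 points of false positives, no other error).
- Control: Po = 1.00, kappa = 1.00.
- Intervention: Po = 0.89, Pe = 0.61 × 0.50 + 0.39 × 0.50 = 0.50, kappa = (0.89 − 0.50)/0.50 = 0.78. The lower limit at n = 69 is about 0.64.
- Pooled: reported 55.5%, database 50%, Po = 0.945, Pe = 0.50, kappa = (0.945 − 0.50)/0.50 = 0.89.
- Pooled lower limit at n = 138: 0.89 − 1.96 × √(0.945 × 0.055/138)/0.50 = 0.89 − 0.076 = 0.814.

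The pooled disagreement is 5.5%, inside the 5.9% that the plan tolerates. At the expected table the pooled rule is met, while the intervention arm alone would miss the same 0.80 mark.

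**4. How often the rule passes.** Simulated samples of 69 + 69 (at least 100,000 per case) were judged by the rule. Background disagreement e, the same in both arms and split equally between false positives and false negatives, was added because the documents do not give its size. Expected pooled kappa is 1 − 2 × (half the over-reporting + e).

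| Background disagreement, both arms | 11 points over-reported: pooled kappa | Rule passes | 5.5 points over-reported: pooled kappa | Rule passes |
|---|---|---|---|---|
| 0% | 0.89 | 64% | 0.945 | 99% |
| 1% | 0.87 | 44% | 0.925 | 92% |
| 2% | 0.85 | 27% | 0.905 | 79% |
| 5.9% | 0.77 | 2% | 0.83 | 14% |

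For comparison, the plan's own design case (kappa 0.88, error equal in both arms) passes in about 54% of samples. So a pass does not separate harmless error from differential error, and neither does a failure.

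**5. What a split by arm would give.** For false-positive proportions of 11% and 0% of each arm, with 69 per arm, the 95% half-width of the difference is 1.96 × √(0.11 × 0.89/69) = 7.4 points.

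**The case against.** The strongest objection is that the 64% figure needs self-report to be otherwise perfect. The protocol does not expect that: its anticipated kappa of 0.88 implies 5.9% disagreement. If that much background error is present and 11 points of over-reporting are added, the expected lower limit is about 0.67 and the rule almost always rejects. A reader might infer that the rule would accept a wholly spurious effect. The documents do not support this: at 1% background the rule already fails at expectation (lower limit 0.788). This objection stands and limits the point.

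A reader might also infer that the trial has no means of telling better use from better reporting. That goes too far. The medication possession ratio is planned from the same database and is objective, although its comparison by arm is not stated.

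Several safeguards are real. Callers are blinded, patients list medications and doses unprompted, and calls in both arms are made on behalf of the cardiologist, so that pressure is common to both. They reduce assessor bias and prompting, but they do not stop a patient who has read the letters from giving the expected list.

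Finally, the article does not make the primary conclusion depend on the kappa, and tabulation by arm could sit in an analysis plan that is not shown. The first is correct. The second does not dispose of the point, because the article itself fixes the measure, the threshold and the sample size, and sizes them on the proportion averaged over arms.

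**Conclusion.** The point holds as a limit on what the stated check can show. One pooled kappa with a lower limit of at least 0.80 cannot reveal whether over-reporting differs by arm, and that is the relevant threat to a self-reported outcome in patients who know they received the letters.

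The size depends on background disagreement, which the documents do not give. Over the range 0% to 5.9%, the chance of passing runs from about 64% down to 2% if all 11 points are over-reporting, and from about 99% down to 14% if 5.5 points are. The rule is thus weakest against partial bias. These figures assume a 69/69 split, a database-defined rate of 50% in both arms among patients aged 65 or over, and background error equal in the two arms. The qualitative conclusion needs none of these assumptions. Nothing in the documents shows that differential over-reporting will occur, or how large it would be.

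**What to change.** - Keep the pooled kappa as a descriptive figure, and state that meeting 0.80 does not validate the between-arm comparison.
- Draw the validation sample balanced by arm.
- Report false-positive and false-negative rates (or sensitivity and specificity) against the Ontario Drug Benefit data by arm, with the between-arm difference and its 95% CI.
- Report the database-defined outcome and the already planned medication possession ratio by arm in linked patients aged 65 or over, as a supportive analysis.
- Interpret the primary result in light of these estimates.

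The cost is mainly wording and tabulation, since the same 138 patients and the same database serve. Precision is limited: about ±7 points at 69 per arm, against a target effect of 11. The check covers only patients aged 65 or over, whose drug coverage differs from that of younger patients. A positive trial may need a more cautious conclusion. A larger linkage request would improve precision but is optional; the planned precision within each arm would take about 138 per arm, or 276 in total.
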